#### Exclusion criteria

1. Hip pain due to other disorders (e.g. trochanteric bursitis, avascular necrosis, pain referred from back).

2. Intra-articular corticosteroid injection into the affected hip or ipsilateral trochanteric bursa injection within the preceding 3 months.

3. Any previous surgery on the affected hip.

4. Clinical suspicion of local or systemic sepsis or infection.

5. Current or previous infection of the affected hip.

6. Significant trauma to the affected hip requiring immobilisation in the previous 3 months.

7. Unwillingness to undergo study interventions.

8. Unable to understand and complete self-report questionnaires written (or spoken) in English.

9. Significant illness (known or suspected) including, but not limited to:

• inflammatory joint disease (e.g. rheumatoid arthritis, seronegative spondyloarthropathy (ankylosing spondylitis, psoriatic arthritis, reactive arthritis, inflammatory-bowel disease associated inflammatory arthritis)).

• polymyalgia rheumatica or other condition requiring regular oral steroid use.

• malignancy (where malignancy is thought to be causing hip pain e.g. suspected bony metastases).

• any other severe medical illness which in the opinion of the local Principal Investigator (PI)(or other authorised clinical delegate) precludes trial participation.

10. Pregnant or lactating females.

11. Receiving anticoagulants (warfarin, dabigatran, rivaroxaban, apixaban or low molecular weight heparin), ritonavir or cobicistat [Amended, see Table 1].

12. Any history of hypersensitivity to triamcinolone acetonide or 1% lidocaine hydrochloride or any of their excipients (1 N Hydrochloric Acid QS, 1 N Sodium Hydroxide QS, Benzyl alcohol. Polysorbate 80, Sodium carboxymethylcellulose and Sodium chloride).

13. Any contraindications to the use of 1% lidocaine hydrochloride as listed in Summary of Product Characteristics (SPC) e.g. complete heart block, hypovolaemia, porphyria [Amended, see Table 1].

#### Patient identification

Potential participants are identified via three routes:GP referrals of patients with hip pain into participating NHS musculoskeletal services at two locations. Local GPs are informed that the trial is taking place and encouraged to refer patients whom they feel may be eligible to participate. Pop-up electronic reminders are incorporated into GP electronic record systems to remind GPs if they enter a code for hip pain or OA during a primary care consultation. Patients are triaged into dedicated musculoskeletal hip research clinics and are sent the Participant Information Leaflet (PIL) prior to their appointment.Patients who have not been directly booked or triaged into the musculoskeletal hip clinic, but who have been referred for management of hip OA to other musculoskeletal, rheumatology and orthopaedics clinics are also identified at their initial appointment. Those deemed to be eligible and interested are given a PIL by the treating clinician.The electronic records of GP practices in the local clinical research network are searched to identify patients consulting with hip pain in the last 12 months. This search is conducted periodically, within small groups of local practices in order to invite consulters with hip pain to the musculoskeletal hip clinic. The search will generate a list of NHS numbers which are screened so that those individuals who have already been referred to the musculoskeletal hip clinic can be excluded. Those who have not already been referred into the service are sent a PIL and a letter inviting them to telephone the Keele Clinical Trials Unit (CTU) if they are interested in attending the musculoskeletal hip clinic. Those who telephone the CTU administrator will receive a brief, provisional eligibility screening. Those who are eligible at this stage are made an appointment for the musculoskeletal hip clinic.

#### Participant screening

Patients identified by routes 1 and 2 above will attend for their routine clinic appointment, according to normal NHS clinical attendance procedures. For patients identified by route 3, a brief, provisional eligibility screen will have been carried out over the telephone by the CTU administrator prior to the appointment being made and a preliminary informed consent to ‘screening assessment’ are taken prior to any eligibility assessment.

The clinical consultation is undertaken by the local PI (or authorised delegate). In accordance with the UK Clinical Trial Regulations, a patient’s eligibility to participate in the trial is the responsibility of a medically qualified doctor. All patients presenting with painful hip OA are considered for inclusion and an Eligibility Screening Form completed.

Patients who have not had a hip radiograph in the past 24 months will undergo radiography as part of eligibility screening. For patients identified via routes 1 and 2 this is in line with usual clinical practice and normal procedures in the musculoskeletal clinic. For patients identified via route 3, radiographs are obtained as a study procedure if they have not had a radiograph performed in the last 24 months. The preliminary consent to ‘screening assessment’ is performed prior to these radiographs being obtained.

Anteroposterior (AP) pelvis and lateral oblique views are obtained as detailed below.

AP pelvis: The patient lies supine on the table with their legs extended and their head resting on a pillow. The median sagittal plane (MSP) is at 90 degrees to the table top and the anterior superior iliac spines (ASISs) are at equal distance from the table-top. The arms are raised onto the pillow. The legs are slightly internally rotated to bring the necks of femora parallel to the table-top. Gonad protection is applied if appropriate. The beam is centred in the midline, midway between the ASIS and the upper border of the symphysis pubis.

Lateral oblique hip: From the initial AP pelvis position the patient is rotated laterally through 45 degrees onto the side under examination and supported in this position with foam pads. The knee and hip are flexed and externally rotated to bring the lateral aspect of the thigh in contact with the table-top. The arms are rested on the pillow. Gonad protection is applied. The beam is centred to the femoral pulse.

#### Recruitment and consent

Eligible patients who are interested in trial participation are invited by the local PI (or authorised delegate) to see a researcher or research assistant who will explain the trial in full. The researcher or research assistant will have received appropriate training and be authorised on the site trial delegation log. Patients are able to ask questions about study involvement. Those who remain interested in participation after seeing the researcher are consented by a researcher, complete baseline data collection, undergo randomisation and receive the intervention during the same clinic visit.

Documented reasons for ineligibility or declining participation are monitored by the Keele CTU as part of a regular review of recruitment progress.

Patients who decline assessment of eligibility, who are either ineligible to participate or who do not wish to participate are thanked for their attendance and instructed to consult their GP should their symptoms continue (route 3) or managed as per usual care (routes 1 and 2).

### Randomisation

#### Allocation

Participants are randomised by an administrator in clinic after consent, baseline data collection and delivery of best current treatment in a 1:1:1 ratio, via the Keele CTU’s web-based randomisation service. This is a secure web-based randomisation system with emergency telephone back-up. The randomisation sequence is computer-generated. Once randomised, the authorised staff member is notified of the participant’s treatment allocation.

#### Allocation concealment

Concealment of the allocation process is ensured through the remote computer-generation of the randomisation sequence and web-based interface including entry of participant details and necessary consent prior to a unique participant identification number being generated and disclosure of treatment allocation.

#### Sequence generation

Blocking (of individual participants) is used as the unit randomisation method to ensure similar numbers of participants are allocated to the three treatment arms. Random permuted block sizes of 3 and 6 are used to give 96 possible randomisation sequences (for each unit of randomisation) with equal chance (determined using a computer-generated random function). The sequence is held within the computer system and not known to researchers/administrators so as to preserve concealment integrity, and hence comparability of participant allocation between study arms.

#### Blinding

Participants and clinicians will not be blind to allocation to best current treatment only (I1) or injection (I2 or I3). However, for those participants randomised to either of the two injection arms, participants are blind to the exact nature of the injection (triamcinolone acetonide plus 1% lidocaine hydrochloride or 1% lidocaine hydrochloride alone) to ensure the validity of the 1% lidocaine hydrochloride injection as a credible placebo. The Research Nurse will remain blind to treatment allocation to enable the nurse who conducts Minimum Data Collection (MDC) to remain unaware of allocation. The statistician will also be blind to treatment allocation. The qualitative researcher is blind to injection group allocation.

Those injected are informed to carry a trial information card at all times during the first 2 months and to present it to medical staff should they be admitted to hospital during their participatory period (6 months). 24-h emergency unblinding is available.

### Interventions

The interventions are delivered in the context of a ‘one-stop’ clinic where assessment, baseline data collection, randomisation and intervention all occur within the same visit.

If bilateral symptoms are present, the hip with the most severe symptoms according to the participant is treated. In the event that both hips are equally affected, the participant is asked to choose which hip to treat. The contralateral hip may be treated in accordance with local guidelines (excluding intra-articular hip injection). Any treatment to the contralateral hip does not constitute trial treatment and is captured through the participant follow-up questionnaires.

#### Intervention arm 1 (I1): Best current treatment

Participants randomised to this intervention receive written information (the Arthritis Research UK Osteoarthritis leaflet [19] and a bespoke HIT trial leaflet on exercise and functional activities), and personalised advice and information about weight loss, exercise, footwear, walking aids and optimising pain management, delivered by the PI (or authorised delegate) within the clinic visit.

#### Intervention arm 2 (I2): Best current treatment plus intra-articular injection of corticosteroid plus lidocaine

Participants randomised to this intervention receive best current treatment as I1 plus one ultrasound-guided intra-articular injection of 40 mg triamcinolone acetonide and 4mls 1% lidocaine hydrochloride into the hip.

Both triamcinolone acetonide 40 mg/ml sterile, aqueous suspension and 1% lidocaine hydrochloride 10 mg/ml solution for injection are prepared and handled in line with manufacturer’s recommendations as outlined and in accordance with the SPC.

A disposable 25G needle and syringe is be used for regional anaesthesia of the skin and superficial soft tissues and a 22G spinal needle and syringe is used for regional anaethesia of deeper soft tissues and intra-articular injection.

The following technique is observed when applying intra-articular injections:

Preparation for the injection includes: LOGIQ ultrasound system with a 1-4 MHz curvilinear transducer (GE Healthcare, Hatfield, England); disposable sterile transducer sheath; disposable 25G needle for regional anaesthesia of skin and superficial soft tissues, and disposable 22G spinal needle for regional anaesthesia of deeper soft tissues and intra-articular injection. Three syringes are prepared containing: 3mls 1% lidocaine hydrochloride; 4mls 1% lidocaine hydrochloride and 1 ml 40 mg triamcinolone acetonide.

A sterile aseptic technique is observed. The participant lies supine with legs extended into a neutral position of comfort. The skin is cleaned with chlorhexidine 0.5% solution. The transducer is covered with gel and a sterile sheath. Sterile gel is applied to the external surface of the sheath. The anterior capsule of the hip joint is located using ultrasound guidance and 3mls 1% lidocaine hydrochloride is introduced to the overlying skin and superficial soft tissues using a 25 g needle. A 22G spinal needle will then be inserted, observing its route in real-time by ultrasound, until its tip is seen to enter the anterior joint capsule. 1 ml of 1% lidocaine hydrochloride is injected into the hip to confirm correct placement and 40 mg of triamcinolone acetonide (1 ml volume) with a further 3mls of 1% lidocaine hydrochloride is injected showing distension of the capsule by the fluid under ultrasound (total intracapsular volume 5mls). The needle is withdrawn, haemostasis ensured and a dressing applied over the injection site. Participant should be advised to wait 15 min following injection or alternatively ensure that they are accompanied by a responsible adult for that time. Participants are advised to observe minimal weight-bearing for 24 h following the injection, and not to drive for 24 h.

It is understood that there may be slight variations to the described technique due to previous training. All injectors will undergo trial-specific training in injection technique and there is a standard operating procedure in place.

#### Intervention arm 3 (I3): Best current treatment plus intra-articular injection of lidocaine

Participants randomised to this intervention will receive one ultrasound guided intra-articular injection of 5mls 1% lidocaine hydrochloride into the hip plus best current treatment.

The injection procedure is conducted as described above (I2) with two exceptions. Three syringes are prepared containing: 3mls 1% lidocaine hydrochloride; 4mls 1% lidocaine hydrochloride and 1mls 1% lidocaine hydrochloride. 1 ml of 1% lidocaine hydrochloride is injected into the hip to confirm correct placement and a further 4mls of 1% lidocaine hydrochloride is then injected showing distension of the capsule by the fluid under ultrasound (total intracapsular volume 5mls).

Injections are delivered by clinicians (2 Consultant rheumatologists, 2 Extended Scope Physiotherapists and one Consultant musculoskeletal sonographer) who are fully trained in the technique and work in the musculoskeletal services. Since musculoskeletal ultrasound is highly operator-dependent and relies on robust training with direct supervision to gain clinical competency, clinicians performing US-guided injections have extensive clinical experience performing US guided injections and will have their competency assessed by a Consultant musculoskeletal sonographer prior to commencement of the trial.

### Crossover and post-trial care

Participants cannot cross over from one arm of the trial to the other. If a participant declines injection after randomisation, this is recorded as a protocol deviation and the participant’s data included in the Intention-to-Treat (ITT) analysis. Similarly, if a participant in the best current treatment arm (I1) of the trial receives an injection as part of standard care they are managed as a protocol deviation and included in ITT analysis.

Participants’ clinical care after the ‘one-stop’ research clinic returns to usual NHS healthcare.

### Outcomes

The primary endpoint is patient-reported hip pain intensity over the whole of 6-months follow-up (through repeated measures at 2 weeks, 2 months, 4 months and 6 months) post-randomisation).

Secondary endpoints are at each of the individual follow-up points (i.e. 2 weeks, 2 months, 4 months and 6 months post-randomisation).

#### Primary outcome measure

Patient-reported hip pain intensity measured using a 0–10 Pain Numeric Rating Scale for current hip pain (hip pain today) [20].

#### Secondary outcome measures

The secondary outcomes include pain, stiffness and everyday physical function (Western Ontario and McMaster University Arthritis Index (WOMAC v 3.1)) [21], participants’ self-reported global impression of change [22], general health (SF-12, EQ-5D-5 L) [23, 24], sleep disturbance (adapted from Dawson et al. [25]), pain self-efficacy [26], illness perceptions [27], maintenance of and return to desired activities including work and social life, healthcare utilisation including medication use and participant incurred cost, treatments received (including referral for surgery and analgesia), participants’ satisfaction with treatment, work (employment status, performance, absence), joint replacement surgery (National Joint Register). Table 2 summarises the content of the participant questionnaires.

**Table 2 Tab2:** Participant Questionnaire Content

Visits	Baseline	2-week	2-month	4-month	6-month
Baseline measures					
Demographics (date of birth, gender)	✓	✓	✓	✓	✓
Demographics (marital status)	✓				
Hip pain questions: uni/bilateral, duration	✓				
Previous hip injection	✓				
Participant treatment preference and expectations	✓				
Comorbidity	✓				
Self-reported height and weight (BMI)	✓				✓
Other musculoskeletal pain (Body manikin) [22]	✓				
Anxiety and Depression – GAD and PHQ8 [23, 24]	✓				
Primary Outcome measure					
Pain - Numerical Rating Scale score for current pain [20]	✓	✓	✓	✓	✓
Secondary outcome measures					
Function - Western Ontario and McMaster University Arthritis Index (WOMAC v3.1) [32]	✓		✓	✓	✓
Participant’ self-reported global impression of change [33]		✓	✓	✓	✓
General health (SF-12) [34]	✓		✓	✓	✓
Sleep disturbance (Likert type scale, adapted from Dawson et al. [35])	✓		✓	✓	✓
Pain self-efficacy [36]	✓		✓	✓	✓
Modified Brief Illness Perceptions Questionnaire [37]	✓		✓		✓
Satisfaction and experience			✓		✓
Health Economic Outcomes					
Health status - EQ5D-5 L [38]	✓	✓	✓	✓	✓
Employment status	✓				✓
Performance at work	✓		✓		✓
Absenteeism from work	✓		✓		✓
Health care utilisation			✓		✓
Participant -incurred costs			✓		✓
Process Data					
Other hip injections received			✓		✓
Self-reported adverse events		✓	✓		
Adherence to best current treatment advice			✓	✓	✓

### Adverse events

Triamcinolone acetonide and 1% lidocaine hydrochloride have specific licenses for the treatment of osteoarthrosis (osteoarthritis) and regional anaesthesia specifically and have been widely used for many years in standard practice in both primary and secondary care and have very well-established and understood safety profiles [21]. They are being used in accordance with the guidance given in the British National Formulary (BNF) and Map of Medicine guidance for injection in hip OA [9, 10]. The incidence of adverse predictable undesirable side-effects associated with the use of corticosteroids correlates with the relative potency of the drug, dosage, and timing of administration and duration of treatment, and therefore based on the dosage to be used in this study, there is no requirement to record non-serious adverse events beyond normal clinical practice. The following events will not be recorded as Serious Adverse Events (SAEs) within this trial:

Hospitalisation for:Routine treatment or monitoring of hip OA associated with any deterioration in conditionTreatment which is elective or pre-planned, for a pre-existing condition not associated with any deterioration in conditionProlongation of hospitalisation not associated with an adverse eventAdmission to hospital or other institution for general care, not associated with any deterioration in conditionTreatment on an emergency, outpatient basis for an event not fulfilling any of the definitions for serious as given above and not resulting in hospital admission

Where a SAE or Suspected Unexpected Serious Adverse Reaction (SUSAR) occurs, reporting procedures are in place that are in accordance with good clinical practice guidance and the requirements specified by the Medicines and Healthcare products Regulatory Agency (MHRA). All SAEs are considered by the external monitoring committees.

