#### Trial organisation and monitoring

The Trial Steering Committee met prior to ethics application in order to agree the final protocol, and at agreed time intervals over the course of the pilot trial. An independent Data Monitoring Committee (DMC) approved the protocol and reviews the safety of the trial. Detailed reports focusing on interim safety, recruitment and retention are prepared by Keele CTU at approximately 6 monthly intervals. All data collection, database design, data input and cleaning, as well as trial oversight procedures, are in line with the standard operating procedures of the Keele CTU and the conditions of the grant. Data is centrally monitored for quality and completeness by Keele CTU.

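### The SAE exemption list exempts routine hip OA admissions when the condition has worsened, while its parallel items exempt admissions only when it has not

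*Protocol article*

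**What the plan says.** The protocol article, Methods, Adverse events, opens its list with "The following events will not be recorded as Serious Adverse Events (SAEs) within this trial". The items that matter here all concern hospitalisation:

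- **Hip OA item.** It begins with the word *Routine* and covers "treatment or monitoring of hip OA associated with any deterioration in" condition.
- **Elective item.** It covers elective or pre-planned treatment "for a pre-existing condition not associated with any deterioration in" condition.
- **General care item.** It covers admission for "general care, not associated with any deterioration in" condition.
- **Prolongation item.** It covers a longer stay only where no adverse event is involved.

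The same section says that "there is no requirement to record non-serious adverse events beyond normal clinical practice" and that "All SAEs are considered by the external monitoring committees". Under Trial organisation and monitoring, the independent DMC "reviews the safety of the trial".

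**The concern.** Three items use the same deterioration phrase. Two negate it and the hip OA item does not. The effect is to exempt the admissions in which the hip has got worse, and to give no hip OA exemption to those in which it has not. That is the reverse of how the neighbouring items work.

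Recording as an SAE is what brings an event to relatedness and expectedness assessment, to SUSAR reporting where that applies, and to the committees. In a trial that injects the hip, an admission because that hip has worsened may reflect the natural course of the disease or an effect of the injection. An event that is never recorded as an SAE is not assessed for which of the two it was. Clinicians also know who was injected and who had best current treatment alone (Blinding), so an unclear exemption could be applied differently by arm. Nothing in the article shows that this has happened.

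**Working it through.** The plan gives no figure to reproduce, so the check is on the text.

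**Step 1: wording.** Of the three items with the deterioration phrase, two carry *not* (elective, general care) and one does not (hip OA). The prolongation item also carries *not*, with an adverse event in place of deterioration.

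**Step 2: apply the list as printed, and then with *not* inserted in the hip OA item.**

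| Admission | Hip OA item as printed | Elective item | Hip OA item with *not* |
|---|---|---|---|
| Routine hip OA care, hip worse, elective | Exempt | Condition fails | Not exempt |
| Routine hip OA care, hip worse, not elective | Exempt | Does not apply | Not exempt |
| Routine hip OA care, hip not worse, elective | Not exempt | Exempt | Exempt |
| Routine hip OA care, hip not worse, not elective | Not exempt | Does not apply | Exempt |
| Not routine hip OA care, e.g. joint infection | Not clearly covered | Does not apply if unplanned | Not clearly covered |

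The first row holds the conflict. Hip OA is a pre-existing condition in every participant, so the elective item's condition withholds exemption from this admission while the hip OA item grants it. The second row is exempt under the hip OA item alone. Such admissions are foreseeable: the Discussion says that patients suitable for surgical referral were deliberately not excluded.

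**Step 3: look for a correction or a reason.** No other section restores the missing condition or explains why worsened hip OA should be exempt. Table 1, which lists the key amendments, contains no change to this list.

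**Step 4: look for another route into safety review.**

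- Non-serious events need not be recorded beyond normal practice, so there is no assured fallback.
- Table 2 asks for self-reported adverse events at 2 weeks and 2 months only, whereas Table 3 runs SAE reporting to 6 months.
- Pain NRS is collected at every follow-up, WOMAC at 2, 4 and 6 months, and health care use at 2 and 6 months. Referral for surgery and joint replacement are also secondary outcomes. The article gives none of these a relatedness assessment or a SUSAR route.

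**The case against.** The strongest reply is that the wording may be intended. Sponsors can choose to exempt progression of the disease under study. With *not* inserted, the hip OA item would largely repeat the elective item; without it, it works as a specific exemption beside a general rule. The article cannot settle this. The redundancy would be partial, though: with *not*, the item would still add monitoring and unplanned routine care, which the elective item does not cover. One could also say that meeting any one item is enough, so there is no formal contradiction. On that reading the elective item's condition has no effect for routine care of the one disease that all participants share, and no reason is given.

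It can also be said that this is a condensed article and that the operative SAE procedures lie elsewhere. That is fair as to detail, but here the article states a rule rather than leaving one out.

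Three stronger readings are tempting and are not supported:

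- **Every admission for a worsened hip is lost.** The item is limited to routine care. The exclusion criteria list avascular necrosis as a disorder other than hip OA and treat hip infection separately, so injection harms of that kind are not clearly exempt.
- **Deterioration is hidden from the trial.** It is missing from the SAE record, not from the outcome data described above.
- **The safety conclusion will be falsely reassuring by a known amount.** With an assumed 6-month risk of 2% to 5% in one arm of 68, the expected admissions would be 68 × 0.02 = 1.4 to 68 × 0.05 = 3.4. Those risks have no source in the document, and the exemption applies to all three arms. Reading 0/68 as evidence of low risk would require a report to show a zero row for a category declared unrecorded, and nothing says that it would.

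**Conclusion.** The point holds as an internal inconsistency in a stated safety rule. Read literally, the list keeps routine admissions for worsening of the study hip out of the SAE record, relatedness assessment and the committees' SAE review, and it points both ways when such an admission is elective. The parallel wording suggests a dropped *not*, but that is an inference; full protocol version 6.0 has to be checked. The size of the loss cannot be estimated from the document. The primary endpoint, sample size and main analysis are unaffected. Because the rule decides what enters safety review for the treated joint, it should be settled before safety results are reported.

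**What to change.** Reconcile the hip OA item with the elective and general care items and with full protocol version 6.0. Which reporting rule was meant is for the sponsor to state.

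- **If *not* was dropped from the article only:** correct the article.
- **If it was also dropped from the working documents:** correct the item, the SAE form and the site instructions. Then re-screen any admissions set aside under the printed wording, using the health care use and joint replacement data already collected.
- **If the exemption was intended:** state the reason and resolve the conflict with the elective item. Report hip OA admissions by arm to the DMC and in the safety results, so that the SAE table is not read as covering them.

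The cost is a short text correction, a note to sites and possibly a look-back, or otherwise a stated reason and one extra table by arm. No extra participants or procedures are needed. How many more SAE reports would follow is unknown.
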